### Outcome assessment

The primary outcome measure is the proportion of fallers between the intervention and control groups, while the secondary outcome measure is the rate of falls between the two groups.

Falls diaries with daily entries will be used to record falls occurrences, and will be returned monthly for one year from randomization, as recommended by previous studies
[7]. These diaries are written in the three main languages of Malaysia; Malay, English and Mandarin, due to varying cultural and educational backgrounds. Prompts will be provided in the falls diaries, which include how and when a fall occurred, or if there were injuries sustained after their fall. Participants will be contacted every 2 months by telephone calls to encourage complete diary returns. The participant will be followed-up for one year, and then invited back for a re-assessment using the same baseline parameters. Adherence to interventions will be recorded for sub-analysis.

Additional secondary outcomes will include changes in ECG, postural blood pressure, visual, physical and psychometric assessments from the baseline assessment to one year follow-up.

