### Statistical analysis and power calculation

One hundred and thirty three participants per group (n = 266) will provide an 80% power (α = 0.05) to detect a 40% reduction in the number of individuals who experience falls, assuming that without intervention, 50% of individuals will experience a subsequent fall (based on previous studies of high risk populations)
[40,41], and a 30% drop out rate (accounting for a likely high mortality and morbidity in our participants).

All analysis will be performed on an intention-to-treat basis with the exception of those who have withdrawn or died. Missing data imputations will be performed on variables with high probability of missingness, either by discarding or replacing data with the mean of the observed values for that variable. Fall and injury rates will be assessed using negative binomial model and multiple regression. For secondary outcomes, comparisons will be conducted between the intervention and control groups. Changes within groups from baseline and potential covariates will be examined with multiple regression and paired t-test for normally-distributed continuous data and Kruskall-Wallis for skewed continuous data.

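### Kruskal-Wallis, a test for independent groups, is assigned to paired within-group change in skewed secondary outcomes, and no named method is tied to the promised between-arm comparison of those outcomes

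*Protocol article*

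**What the plan says.** All of this is in the protocol article.

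- **Outcome assessment.** The first-named secondary outcome is a comparison between arms: "the secondary outcome measure is the rate of falls between the two groups". The others are before-after measures on the same participants: "Additional secondary outcomes will include changes in ECG, postural blood pressure, visual, physical and psychometric assessments from the baseline assessment to one year follow-up".
- **Fall rates, under the heading Statistical analysis and power calculation.** The article plans: "Fall and injury rates will be assessed using negative binomial model and multiple regression".
- **Same section, between arms.** "For secondary outcomes, comparisons will be conducted between the intervention and control groups". This sentence names no test or model.
- **Same section, next sentence.** The subject is stated first: "Changes within groups from baseline and potential covariates will be examined with multiple regression". The sentence then divides the tests by the shape of the distribution: "paired t-test for normally-distributed continuous data and Kruskall-Wallis for skewed continuous data".

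**The concern.** The last sentence has change within groups as its subject. It splits the continuous outcomes by distribution: the paired t-test if normal, Kruskal-Wallis if skewed. The first is a test for pairs and the second is a test for independent samples. Used on the baseline and one-year values of one arm, Kruskal-Wallis treats each person's two values as if they came from two different people. The gain from pairing is lost and the p-value no longer means what it says.

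A second gap lies next to this. The sentence that promises the randomised comparison gives no method, while the sentence that gives methods concerns change inside each arm. Within-arm change does not estimate the treatment effect. Participants enter because of two or more falls, or one injurious fall, in the past year, so regression to the mean and ageing can move both arms alike.

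At stake are the analyses of the physical, visual, blood pressure and psychometric outcomes. Real change in skewed measures could be missed, and the article leaves open how the arms will be compared on them.

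**Working it through.** **1. The plan's own figure.** The only computed figure in the section is the sample size. With 50% versus 30% fallers (a 40% relative reduction), two-sided 5% (sidedness is not stated, so this is assumed), 80% power and pooled variance:

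n = [1.96·√(2·0.4·0.6) + 0.8416·√(0.5·0.5 + 0.3·0.7)]² / 0.20² = (1.358 + 0.571)² / 0.04 ≈ 93 per arm.

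Allowing for 30% dropout, 93 / 0.70 = 133 per arm, as stated. The figure is reproduced and this point does not change it. It supplies the 93 completers per arm used below.

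**2. Inputs not in the article.** No correlation between baseline and one-year values is given, nor any effect size for these outcomes. Assumed: correlation ρ of 0.3, 0.5 and 0.7; log-normal (skewed) values; a change of 0.3 SD on the log scale for power.

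**3. Type I error, closed form.** With two samples, Kruskal-Wallis is the rank-sum test, which depends on ranks only. Pairing reduces the true variance of the rank difference to about (1 − ρ_S) of what the test assumes, where ρ_S is the rank correlation. For log-normal pairs, ρ_S = (6/π)·arcsin(ρ/2). The test therefore rejects only when a correctly scaled z exceeds 1.96/√(1 − ρ_S).

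| ρ | ρ_S | 1.96/√(1 − ρ_S) | True two-sided level |
|---|---|---|---|
| 0.3 | 0.288 | 2.32 | 2.0% |
| 0.5 | 0.483 | 2.73 | 0.6% |
| 0.7 | 0.683 | 3.48 | 0.05% |

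**4. Simulation.** 4,000 runs with 93 pairs. Kruskal-Wallis was applied to baseline versus follow-up values, and signed-rank to the paired log differences.

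| ρ | Level, Kruskal-Wallis | Level, signed-rank | Power, Kruskal-Wallis | Power, signed-rank |
|---|---|---|---|---|
| 0.3 | 1.9% | 4.4% | 53% | 66% |
| 0.5 | 0.5% | 5.2% | 51% | 80% |
| 0.7 | 0.05% | 4.9% | 53% | 95% |

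A repeat gave levels of 2.3%, 0.7% and 0.03% for Kruskal-Wallis, power of 51%, 51% and 54%, and the same signed-rank power. The closed form and the simulations agree. The stronger the correlation, the more is lost.

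**5. The between-arm comparison.** Every additional secondary outcome has a baseline value. With equal variance at the two times, the variance of the arm difference, relative to comparing follow-up values alone, is:

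- follow-up value alone: 1.0
- change score: 2(1 − ρ)
- follow-up value regressed on arm and baseline: 1 − ρ²

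At an assumed ρ of 0.6 these are 1.0, 2 × 0.4 = 0.80, and 1 − 0.36 = 0.64. The regression has 20% less variance than change scores (0.64/0.80 = 0.80) and 36% less than follow-up values alone, with no extra data.

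**The case against.** **The randomised comparison is planned.** A reader might infer that the secondary outcomes rest on within-group tests. The article does not support that. Between-arm comparison of secondary outcomes is promised in the sentence just before, and fall rates have a negative binomial model. This stands, and it limits the point to the change-from-baseline outcomes.

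**No side-by-side reading of p-values is proposed.** If both arms changed equally and each within-arm test had 50% power, exactly one arm would be significant in 2 × 0.5 × 0.5 = 50% of trials with no treatment effect. The arithmetic is right, but nothing in the article says that treatment conclusions will be drawn that way. It is a reason to keep within-arm results descriptive, and no evidence of a planned error.

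**Multiple regression is also named, with covariates.** With an arm term and the baseline value it would be the model recommended here, and a condensed article may leave such terms to a fuller plan. This stands in part: the absence of model terms is not the fault. The fault is that the sentence as worded ties the regression to within-group change.

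**Kruskal-Wallis may have been meant for change scores between arms.** With two arms it would equal the rank-sum test and be valid. But the text says within groups and pairs it with the paired t-test, so the valid reading needs words that are not there.

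**The error is conservative.** This is correct. A reader might take the wrong test to mean more false positives; with positively correlated pairs it gives fewer.

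**Conclusion.** Wrong as written, of moderate severity. The article assigns an independent-groups test to paired data. That the level and power fall follows from any positive correlation between baseline and one year; how far they fall depends on the assumed correlations, the assumed 0.3 SD shift and 93 pairs. Under these, the true level is about 2% down to 0.05% or less, and power is roughly 51-54% where signed-rank has 66-95%. Which outcomes will turn out skewed is not known from the article.

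The wider claim, that the secondary analysis as a whole depends on before-after tests, does not hold. What holds is that for the change-from-baseline outcomes every named method is attached to within-group change. The primary outcome, the fall-rate analysis and the 133 per group are unaffected.

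**What to change.** Amend the wording of the statistical section:

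1. Replace Kruskal-Wallis with the Wilcoxon signed-rank test for any within-arm change in skewed data, and report within-arm change as descriptive only.
2. State that the between-arm comparison of each continuous secondary outcome is a regression of the 12-month value on arm and baseline value, reported as an adjusted difference with 95% confidence interval. Where the outcome is skewed, use a transformation or robust or bootstrap standard errors.
3. If Kruskal-Wallis was intended for comparing change scores between the two arms, say so explicitly.

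The cost is a change of text, best made before any unblinded analysis. No new data, visits or participants are needed.

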## Discussion

Multifaceted interventions in previous studies have demonstrated the effectiveness of this approach in reducing falls compared to single or multicomponent interventions
[42]. However, a meta-analysis of multifaceted interventions by the most recent Cochrane review has found that although it reduces the number of falls, multifactorial interventions do not help reduce the risk of falling
[5]. Strong positive outcomes were observed especially in studies with land-based exercise, medication withdrawal, vitamin D supplementation, footwear intervention, and home environment modification
[14,43].

There is however insufficient evidence that multifactorial interventions can be conducted outside a tightly controlled group of research trials and implemented into clinical practice and community services
[42]. There is also a lack of evidence to prove the effectiveness of visual intervention, medications withdrawal and falls prevention education in reducing the number of falls
[14,39]. Most studies were primarily performed in Western countries, and very few RCT’s have been conducted in low and middle-income developing countries, which will be achieving the ‘ageing population’ status in a few decades, at a substantially faster rate than the Western nations
[2,44,45]. Although many falls-related trials have been conducted, interventions or outcomes were rarely implemented in a large-scale clinical setting. Edwards theorized that the baton for falls prevention needs to be passed on by falls experts to medical practitioners for it to be incorporated into common clinical practice. Active participation of the government, policymakers and research funders is also vital
[45,46].

It is also important to take note of ethnicity and also where older fallers are recruited from. Fallers from the Stroke Unit or Accident and Emergency Department are characteristically more dependent, prone to recurring falls, and are more receptive to interventions
[4,46-48]. Lee and colleagues reported 25.2% of 1-year falls incidence when recruiting fallers from medical and community health centers
[4]. A systematic review of worldwide Chinese fallers reported a lower rate of 18%
[49]. The frequently reported incidence rate of 30% annual falls in elderly
[8], may therefore fluctuate depending on faller characteristics.

Cultural diversity may play an important role in falls interventions. Chinese older people residing in London were reluctant to talk about falls, tending to hide falls from their adult children to avoid worrying them; and have poor knowledge about the availability and content of interventions
[13,49]. The results of Western studies should not be directly extrapolated to Malaysia and other Asian countries due to demographic, lifestyle, cultural, environmental and health service system differences. Little is currently known about how falls can be appropriately managed in developing countries. In our setting where the population is ageing at a far faster rate than the Western developed countries, cost-effective solutions to age-related conditions are desperately needed. Hence it is important to evaluate the effectiveness of the falls intervention program on local fallers before developing relevant falls interventions in clinical practice.

Using a pragmatic RCT approach to falls, MyFAIT will evaluate the effectiveness of a multifactorial intervention in reducing the incidence of falls, and the rate of falling as a secondary prevention measure in older fallers seeking medical attention in primary and secondary care settings. This project will fill a vital gap in global falls prevention measures by targeting a culturally-diverse older Asian community of low-middle income. This study will also help to determine the characteristics of fallers in our setting and detect potential differences or similarities between existing falls research populations. If successful, these approaches have the potential for widespread application in geriatric healthcare services and should minimize the projected escalation of falls related health service needs in the future, and improve the quality of life of our older community.

## Conclusion

While multifactorial falls interventions have been demonstrated to be effective in reducing frequency of falls in Western populations and used in many falls intervention program in developed countries, such an intervention has not been adequately evaluated in lower income countries in Asia. We are conducting a randomized-controlled study in a middle-income developing country in South-East Asia. The results of this study will provide much needed information about the potential benefits of multifactorial falls intervention outside the developed countries. This study will also provide valuable information on the characteristics of fallers and the response to individual interventions within the multifactorial program.

## Abbreviations

WHO: World Health Organization; MyFAIT: Malaysian Falls Assessment and Intervention Trial; ICD-10: International Classification of Diseases, 10th Edition; UMMC: University Malaya Medical Centre; TUG: Timed Up-and-Go; ECG: Electrocardiogram; DASS-21: Depression Anxiety Stress Scale; FES-I: Falls Efficacy Scale-International; HOME FAST: Home Falls and Accident Screening Tool; FRID: Falls-risk increasing drugs.
